#### 2.4.1. Radiation Therapy

Patients receive a standard treatment for lung cancer according to the current German guideline [2]. For patients with inoperable locally advanced NSCLC, the treatment often includes fractionated radiation therapy with total doses of 66–70 Gy (dose per fraction = 2.0 Gy) conventionally. It may be combined with concurrent chemotherapy. Depending on the histologic subtype, cisplatin is combined with vinorelbine (squamous cell carcinoma), pemetrexed (adeno-carcinoma), or paclitaxel (both subtypes), followed by consolidation therapy with durvalumab [2]. Some patients with SCLC may be irradiated with daily fractions of 2.0 Gy up to 60–66 Gy. For these patients, radiation treatment is generally combined with four to six courses of chemotherapy, of which two courses are given concurrently. Standard chemotherapy for SCLC includes cisplatin and etoposide [2]. For patients not experiencing progression during radio-chemotherapy, consolidation systemic treatment with durvalumab may be offered. Irradiation may be associated with acute or subacute side effects, which may cause an interruption of the treatment. If the next radiation fraction is delayed for more than 7 days, the principal investigator has to be notified.

#### 2.4.2. Number of Daily Steps

Physical activity will be documented under pragmatic real-world conditions using daily step counts recorded by an already integrated step counter of a patient-owned smartphone or a corresponding health app downloaded prior to the start of radiation therapy. Data are received from the patient’s smartphone for weeks 1 and 5. This pragmatic approach may introduce variability between devices and applications; however, the primary endpoint is based on within-patient change, which partially mitigates between-device differences. Data are extracted by trained members of the trial group to make sure the recorded information is complete and consistent.

To ensure standardized carrying behavior, patients will be instructed to carry their smartphone continuously during waking hours whenever feasible, irrespective of whether they are physically active or not. For each valid day, steps per wear-hour are obtained by dividing the total number of daily steps by the wear-time per day (hours). For a valid day, the wear-time must be 4 h or longer. Daily normalized step counts will be aggregated into weekly averages based on all valid days in the respective week. To be included in the analyses, the corresponding week (week 1 or 5) must include at least four valid days. The wear-time will be obtained from the patient’s smartphone.

#### 2.4.3. “Step Reminder” App

The “Step Reminder” app has been made and will be maintained by Nextlabel Offene Handelsgesellschaft (OHG), Luebeck, Germany. It reminds the patients three or four times per day (patient’s choice) to walk a certain number of steps during the radiotherapy course. In addition, the “Step Reminder” app will record the number of reminders sent per day, the timestamp of each reminder, and any potential user interaction. These parameters will be used as exploratory measures of adherence to the intervention. Nextlabel OHG will also provide the required documentation for the “Step Reminder” app. All rights of the “Step Reminder” app remain with the developing company. For individual activation of the app, the company requires the patient’s e-mail address. To ensure its protection, the sponsor of the APPAREL trial, the University Medical Center Schleswig-Holstein, and the developer of the “Step Reminder” (Nextlabel OHG) app entered into a contract including an approved data protection concept. The sponsor and Nextlabel OHG have neither a role in designing the APPAREL trial nor in handling the data. Nextlabel OHG is involved in the Interreg project Health-Advancing Technology for the Elderly as a project partner, but its role is limited to the production of mobile applications.

#### 2.4.4. Patient Satisfaction with the “Step Reminder” App

Prior to the start of radiotherapy, patients are asked how much they are used to handling a smartphone and whether they require assistance regarding the installation of a health app or the “Step Reminder” app. At the end of week 5, patients randomized to Arm A complete a questionnaire focusing on satisfaction with the app and a potential change of “digital behavior”, for example, with respect to using the internet or other apps to enquire about different aspects of their disease [26,27]. If less than 80% of the patients are satisfied with the “Step Reminder” app, it should be further optimized. If less than 60% of the patients are satisfied, the app is not suitable for the purpose assessed in the APPAREL trial and should be further optimized. The 80% and 60% thresholds are predefined feasibility and acceptability criteria for app optimization. They represent pragmatic operational definitions rather than evidence-based cut-off values and are not statistically derived cut-offs. A satisfaction rate below 80% indicates room for further optimization before broader use, whereas a satisfaction rate below 60% indicates insufficient acceptability for the intended purpose.

#### 2.4.5. Adverse Events

Adverse reactions are rated according to the Common Terminology Criteria for Adverse Events classification 5.0 [28]. Serious and unexpected events have to be indicated within 24 h after their detection to the principal investigator.

### 2.5. Statistics

#### 2.5.1. Sample Size

This prospective randomized study is designed to analyze the effect of the “Step Reminder” app on physical activity during irradiation in lung cancer patients. The primary endpoint is the within-patient change in weekly average steps per wear-hour between the fifth and the first week. The primary analysis includes all randomized patients with evaluable data regarding the primary endpoint. The comparison (“Step Reminder” app group vs. control group) is made with a two-sided Wilcoxon–Mann–Whitney U test.

Calculation of the required sample size considers a clinically relevant difference corresponding to a relative difference in the within-patient change in steps per wear-hour of about 30% between treatment arms. Given the non-parametric nature of the primary analysis, this assumption is interpreted as a moderate shift in the distribution of the endpoint, which represents a probability of superiority of about 0.65. The assumed 30% relative difference represents a pragmatic planning assumption for this exploratory randomized phase 2 trial and should not be interpreted as an established minimal clinically important efficacy difference for this endpoint. Assuming a two-sided significance level of α = 0.05 and a statistical power of 80%, 28 patients are needed to detect such an effect using the asymptotic approximation of the Wilcoxon–Mann–Whitney U test. It is assumed that approximately 10% of the randomized patients cannot be evaluated with respect to the primary endpoint. Therefore, 32 patients need to be randomized. The calculation aligned with the analysis population, and the endpoint definition is considered appropriate for this exploratory study. The multicenter design primarily supports recruitment feasibility and broader applicability of the exploratory findings; it is not intended to imply a confirmatory multicenter efficacy trial. Results are interpreted descriptively and will contribute to the design of additional larger studies.

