## Abstract

**Background**: Radiation therapy with or without systemic treatment for lung cancer can cause adverse reactions, e.g., fatigue. Affected patients may experience a decrease in physical activity and, as a consequence, be unable to receive the complete assigned treatment. Physical exercise may be helpful. A benefit of exercise regarding completion of systemic treatment and quality of life was previously suggested. Irradiated patients may benefit as well. A smartphone-based app reminding patients to make a minimum number of steps might positively influence physical activity. The prototype of an app called “Step Reminder” was recently finalized. The randomized APPAREL trial (NCT07627022) evaluates whether this app can improve physical activity during irradiation for lung cancer. **Methods**: The primary endpoint of this phase 2 trial focuses on the within-patient change regarding the mean number of daily steps (week 5 minus week 1). Secondary objectives include satisfaction with the application and its impact on the perception of digital health technology. Patients are randomized 1:1 to be treated with a standard approach (conventionally fractionated irradiation with or without systemic treatment) supported by the “Step Reminder” app (Arm A) or standard treatment without the app (Arm B). The app provides reminders several times per day to walk a pre-defined number of steps. To make sure that the required 28 patients are included in the primary analysis population (full analysis set), 32 patients have to be randomized. **Results**: At this stage, results are not available. **Conclusions**: It is expected that the app will have a positive effect on the patients’ physical activity (number of steps).

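### 28 evaluable patients give about 27% power at a probability of superiority of 0.65, not the stated 80%; that effect needs about 117

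*Protocol article*

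**What the plan says.** Section 2.5.1 (Sample Size) of the protocol article gives a complete set of inputs.

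- **Test:** the comparison of the arms "is made with a two-sided Wilcoxon–Mann–Whitney U test".
- **Error rate:** "Assuming a two-sided significance level of α = 0.05".
- **Effect:** in words, "a relative difference in the within-patient change in steps per wear-hour of about 30% between treatment arms". This is then translated into a moderate distributional shift, "which represents a probability of superiority of about 0.65".
- **Result:** "a statistical power of 80%, 28 patients are needed to detect such an effect using the asymptotic approximation" of that test.

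The section then allows for about 10% non-evaluable patients and arrives at 32 randomized. The abstract repeats the number as a requirement: "To make sure that the required 28 patients are included in the primary analysis population". Section 2.3 sets 1:1 randomization. The abstract, section 2.2 and the Discussion make clear that 28 and 32 are totals over both arms.

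**The concern.** A probability of superiority of 0.65 is a moderate effect. Under normal data it is a shift of 0.545 SD. Fourteen patients per arm cannot detect a shift of that size with 80% power in a two-sample test, so the figure invited a check.

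Two things are at stake. First, the article credits the design with a property it may not have. Section 2.5.2 keeps a two-sided 0.05 test and labels only the p-values beyond the primary analysis as descriptive, so the primary p-value will be read against the stated power. A reader who believes in 80% power could take a non-significant result as evidence against the app. Second, section 2.5.1 says the results will feed into larger trials. A later trial that reused this calculation would inherit the same shortfall.

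**Working it through.** **Inputs**

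- Two-sided α = 0.05, so z = 1.960 (section 2.5.1)
- Power 80%, so z = 0.842 (section 2.5.1)
- Probability of superiority P = 0.65, so P − 0.5 = 0.15 (section 2.5.1)
- Allocation 1:1, so c(1 − c) = 0.25 (section 2.3)
- Evaluable total N = 28, i.e. 14 per arm (section 2.5.1, abstract)

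The 30% relative difference cannot be used as an input, because the article gives neither a control-arm change nor an SD. The value 0.65 is the only effect figure that fits the named formula.

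**Attempt to reproduce 28.** Noether's asymptotic formula for this test is

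N = (z₀.₉₇₅ + z₀.₈₀)² / [12 · c(1 − c) · (P − 0.5)²]

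(1.960 + 0.842)² = 7.849, so N = 7.849 / (12 × 0.25 × 0.0225) = 7.849 / 0.0675 = **116.3**. That is 117, or 118 with equal arms.

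The 28 does not reproduce. Only the dropout step does: 28/0.9 = 31.1, rounded up to 32.

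**Power with 28 evaluable patients**

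- Noether: Φ(√(3 × 28) × 0.15 − 1.960) = Φ(1.375 − 1.960) = **27.9%**
- With the exact null variance: SE = √(29/(12 × 196)) = 0.111, and Φ(0.15/0.111 − 1.960) = **27.1%**
- Simulation of the test at 14 per arm (20,000 runs each; normal, logistic, Laplace and exponential data; with and without continuity correction): **25% to 28%**
- If all 32 randomized patients were evaluable: Φ(√96 × 0.15 − 1.960) = 31%

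As a check on the formula, simulated power is 80% to 82% at 58 or 59 per arm, which confirms a total of about 117.

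**Other readings of the stated inputs**

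| Reading | Result |
|---|---|
| 28 per arm (56 in total) | 49% power |
| One-sided 5% test | 92 patients needed; 39% power at 28 |
| 0.65 as a rounded value (0.645 to 0.654) | 125 to 111 patients needed |
| Comparison of means at a shift of 0.545 SD | 53 per arm, 106 in total; 30% power at 14 per arm |

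None comes near 28 patients with 80% power.

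**What 28 patients can detect.** Solving the formula for P gives 0.5 + √(7.849/84) = 0.806. Simulation with normal data at 14 per arm (8,000 runs) gives 79% power at a shift of 1.15 SD (P = 0.79) and 83% at 1.2 SD (P = 0.80). The detectable effect is therefore P of about 0.80, a shift of about 1.2 SD, which is 1.2/0.545 = 2.2 times the planned one.

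**Precision.** Under normal data, the half-width of the 95% interval for the shift is about 1.96 × √(2/14)/√0.955 = 0.76 SD, wider than the planned effect of 0.545 SD.

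**Source of the slip.** The article does not reveal it. Leaving out the factor 0.25 gives 7.849/(12 × 0.0225) = 29.1. A one-sample normal calculation at 0.545 SD gives 26.4. Neither yields exactly 28, and the finding does not depend on the explanation.

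**The case against.** The strongest reply is that little hangs on this number. Section 2.5.1 calls the trial exploratory and the 30% a pragmatic planning value. Section 2.5.3 says the results are interpreted descriptively only. The Discussion lists the small sample among the major limitations and calls the results mainly hypothesis-generating. No go/no-go decision rests on the primary p-value; the only decision thresholds are the satisfaction rates in section 2.4.4. A Hodges–Lehmann estimate with a 95% confidence interval is already planned. The link between the 30% and 0.65 may also be set out in the full protocol, which is not shown.

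Much of this is fair. It makes misuse of a null result less likely, and the missing basis for the 30% should not be counted as a separate defect. But these caveats concern whether the effect size is justified and how cautiously to read the results. None of them qualifies the statement that 28 patients give 80% power, and none says that a non-significant primary result would be uninformative. Section 2.5.1 goes on to call the calculation appropriate. Condensation of a longer document is no explanation either: the article prints the test, error rate, power, effect and sample size, and they do not agree.

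**Conclusion.** The power statement is wrong as written. At the planned probability of superiority of 0.65, 28 evaluable patients give about 27% power instead of 80%, and 80% would need about 117 evaluable patients, roughly four times as many. Allowing for 10% non-evaluable, that is 130 randomized (117/0.9), or 132 with equal arms (118/0.9 = 131.1, rounded up).

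The conclusion rests only on inputs stated in the article. Simulated power at 14 per arm hardly moves across the four distributions tried. The normal model is needed only to express effects in SD units. The statement must be corrected, although the exploratory purpose means that the trial can still run at its planned size.

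**What to change.** Keep the 32 patients and correct the claim. In section 2.5.1, delete the statement that 28 patients are needed for 80% power at 0.65 and replace it with wording such as:

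> The sample size of 32 randomized patients is set by feasibility. With 28 evaluable patients, the two-sided 5% Wilcoxon–Mann–Whitney test has about 27% power at a probability of superiority of 0.65 and reaches 80% power only at about 0.80. Detecting 0.65 with 80% power would need about 117 evaluable patients. A non-significant result is not evidence that the app has no effect.

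The sponsor must confirm that feasibility is the true basis, since the article currently derives the number from power. If it is not, the alternatives are to plan openly for an effect of about 0.80 and justify it, or to enlarge the trial.

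The abstract should no longer present 28 as a required number. It would also help to report the estimated probability of superiority with its 95% confidence interval next to the Hodges–Lehmann estimate, because planning used that scale.

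The cost is wording in section 2.5.1 and the abstract, and in the registry entry if it repeats the claim. No extra patients are needed. The stated power becomes less favourable.

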#### 2.5.2. Statistical Aspects

The full analysis set includes all randomized patients who provide evaluable data for the primary endpoint. Evaluable data are defined as at least one valid week of step count data, i.e., a week with at least four valid days (valid day = at least 4 h of smartphone wear-time). Patients without evaluable data in either week 1 or week 5 will be excluded from the primary endpoint analysis. This definition ensures a reliable estimation of weekly average steps per wear-hour and is considered appropriate considering the nature of the digital endpoint and the exploratory design of the APPAREL trial. The full analysis set is not intended to represent a strict intention-to-treat population; it includes randomized patients with evaluable primary endpoint data. The number of randomized patients excluded from the full analysis set and the reasons for exclusion will be reported by treatment arm. A Consolidated Standards of Reporting Trials (CONSORT) flow diagram will be provided explicitly reporting the number of randomized patients excluded from the primary analysis, along with detailed reasons for exclusion in each treatment arm.

The per-protocol set is defined as a subset of the full analysis set, including patients without major protocol deviations, with adequate adherence to study procedures, and with sufficient and consistent data quality. In addition to meeting these criteria, patients of the per-protocol set must demonstrate adequate compliance with smartphone use and adherence to the assigned treatment. For Arm A, this means documented use of the “Step Reminder” app during the majority (≥80%) of the first five weeks of the radiation therapy period. For Arm B, this means no use of any comparable reminder app or structured activity intervention.

Statistical analysis is based on observed cases only. Patients must meet the predefined criteria for valid data in week 1 and week 5 to be included in the primary analysis. Missing data, if any, may be expected to be not missing completely at random, particularly in relation to insufficient smartphone wear time. Therefore, the extent and patterns of missing data will be described descriptively, and reasons for non-evaluable data will be summarized. Because of the small sample size and the exploratory nature of the APPAREL trial, no formal imputation and no best-case, worst-case, or model-based missing-data sensitivity analyses will be performed. The predefined approach for missing primary endpoint data is restricted to complete-case analysis, and the results are interpreted in light of the observed missing data structure. The per-protocol set is analyzed using the same statistical methodology as for the primary analysis. Results from the per-protocol set are considered supportive and will be used to assess the consistency and robustness of the findings in the full analysis set. Statistical tests are performed as two-sided tests with a nominal significance level of α = 0.05. Given the exploratory nature of this randomized trial, no adjustment for multiplicity is applied, and *p*-values beyond the primary endpoint analysis are interpreted descriptively. All secondary, subgroup, adjusted, and sensitivity analyses will be interpreted descriptively. Nominal *p*-values from these analyses will not be interpreted as confirmatory.

All available data will be used irrespective of adherence to the assigned treatment, including non-use or discontinuation of the reminder app, provided that sufficient data are available for endpoint calculation. Exploratory adjusted analyses may be performed to account for potential baseline imbalances, including baseline physical activity and the stratification factor (concurrent systemic treatment: yes vs. no). These analyses can be interpreted as supportive. Fatigue, pain, distress, and performance status will be summarized descriptively and may be explored in supportive analyses to contextualize changes in physical activity. They are not included as mandatory covariates in the primary model due to the small sample size and the risk of overfitting.

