## 3. Discussion

Radiation therapy or radio-chemotherapy for locally advanced lung cancer can lead to significant fatigue and a subsequent decrease in physical activity [20,21]. This process may have a remarkable negative effect on the patient’s quality of life and treatment outcomes [9,10,11,12,13,14,15,16,17,18,19]. These impairments may be alleviated by means of regular physical exercise before and during the phase of treatment [8,9,10]. However, when significantly stressed by anticancer treatment and its toxicity, both motivation and ability to regularly perform training sessions and workouts may be limited. Promising approaches to improve this situation include participation in group exercise or yoga programs and physiotherapy. However, depending on the patient’s place of residence and potential waiting lists, these options may not always be available when needed. One can imagine that an app installed on a patient’s smartphone, reminding the patient daily to perform some physical exercise or to walk a minimum number of steps, could also be a valuable support. Such an app called “Step Reminder” is already available but has not yet been tested in patients. In the field of radiation therapy, apps are becoming increasingly popular to support patients [29,30,31,32]. The clinical value of the “Step Reminder” app is evaluated in patients irradiated for lung cancer in the current APPAREL trial. Ideally, this randomized trial will show that the “Step Reminder” app has a positive effect on the patient’s average step count during the period of treatment. However, when interpreting the results of the APPAREL trial after its completion, the corresponding limitations have to be considered. Major limitations include the exploratory nature of the trial and the comparably small sample size of 32 patients. Due to the limited sample size, analyses aiming to determine whether effects are different between subgroups related to baseline characteristics, number of daily reminders chosen by the patients, pain, fatigue, and items addressed in the NCCN distress thermometer [27,28] can only contribute to the generation of hypotheses and to designing future prospective trials. Another important limitation is the fact that suitability for the APPAREL trial includes smartphone ownership and sufficient digital literacy. Therefore, the study may not represent many elderly or frailer patients irradiated for lung cancer. Further limitations include the open-label study design, device and application heterogeneity, potential missing-not-at-random endpoint data, attrition bias due to evaluability criteria, assessment of activity only during weeks 1 and 5, and the possibility of contamination in the control arm through independent use of activity apps or wearable devices. Blinding was considered not feasible in this pragmatic phase II setting, because the intervention consists of active use of a reminder app. The primary endpoint is based on automatically recorded step counts rather than investigator-rated activity, which reduces but does not eliminate behavioral bias. The control arm receives standard care without an app; potential performance effects and increased attention in the intervention arm will be considered when interpreting the results. Moreover, since participants in the intervention arm receive repeated reminders throughout treatment, behavioral changes may partly reflect increased attention (Hawthorne effect) rather than the intrinsic efficacy of the reminders themselves. Unfortunately, it is not possible to eliminate the possibility of this effect in the APPAREL trial.

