## Figures and Tables

**Table 1 jcm-15-05678-t001:** Assessments at the time of screening, at baseline, and during radiation therapy.

	Screening	Baseline	End of Week 1 of Radiation Therapy	End of Week 5 of Radiation Therapy
Demographics	X			
Medical history and medication		X	X	X
Patient and tumor characteristics		X		
Performance status		X	X	X
Assessment of distress		X		
Assessment of pain		X		
Assessment of fatigue		X		
Details of radiation therapy	X			
Radiation therapy performed as planned?			X	X
Written informed consent given	X			
Fulfillment of inclusion criteria	X			
Expected non-compliance	X			
Wear-time of the smartphone			X	X
Number of steps per day			X	X
Handling smartphones		X		
Satisfaction with the “Step Reminder” app				X
Influence of using health technology				X

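### The per-protocol set drops patients in a structured activity programme from Arm B only, which tilts this supportive check towards the app

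*Protocol article*

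**What the plan says.** In section 2.5.2 the per-protocol set is drawn from the full analysis set, with some conditions that both arms share: "including patients without major protocol deviations, with adequate adherence to study procedures, and with sufficient and consistent data quality". These shared conditions do not mention activity support from outside the trial. Adherence to the assigned treatment is then spelled out by arm:

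- Arm A: "For Arm A, this means documented use of the “Step Reminder” app during the majority (≥80%) of the first five weeks of the radiation therapy".
- Arm B: "For Arm B, this means no use of any comparable reminder app or structured activity intervention".

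On the method, the section states: "The per-protocol set is analyzed using the same statistical methodology as for the primary analysis". That is the unadjusted two-sided Wilcoxon–Mann–Whitney test. The results are called supportive and "will be used to assess the consistency and robustness of the findings in the full analysis set". The Discussion lists among its limitations "the possibility of contamination in the control arm through independent use of activity apps or wearable devices". It says nothing on the same behaviour in Arm A, and no text in the article forbids it there.

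**The concern.** The Arm B sentence joins two different things. Use of a comparable reminder app by a control is crossover to something like the assigned intervention, and removing crossovers is usual in a per-protocol set. A structured activity programme is a co-intervention that a patient in either arm can take up. The Discussion itself names group exercise, yoga and physiotherapy as promising options. The rule acts on that co-intervention in one arm and ignores it in the other.

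The direction follows from the trial's own premise that exercise supports activity. Removing programme users from Arm B lowers the control mean change, and leaving them in Arm A keeps its mean where it was. At stake is how the supportive result is read. A per-protocol estimate that agrees with the full-analysis-set estimate, or exceeds it, could be taken as reassurance when part of the agreement comes from the set definition.

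**Working it through.** The plan gives no figure for this bias, so there is nothing to reproduce. The asymmetry is established by reading the two arm-specific criteria side by side. The arithmetic only shows how large the effect could be.

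**Inputs from the protocol article**
- Allocation 1:1 (section 2.2).
- 28 evaluable patients, probability of superiority 0.65, two-sided α = 0.05 (section 2.5.1). I take 14 per arm before per-protocol exclusions.

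**Assumed inputs (not in the document)**
- q: share of each arm that starts a structured activity programme after week 1.
- s: gain in the week 5 minus week 1 change among those patients, in SD.
- q and s are equal in the two arms, the app has no effect, and the data are normal.

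**Planning shift on the SD scale**

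√2 × Φ⁻¹(0.65) = 0.545 SD.

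**Bias from the one-sided exclusion**

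Arm A keeps its users, so its mean change is raised by q × s. Arm B loses its users, so its mean is raised by 0. The expected difference A − B is q × s, and P(A > B) = (1 − q) × 0.5 + q × Φ(s/√2).

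| q | s | Bias q × s | Share of 0.545 SD | P(A > B) |
|---|---|---|---|---|
| 10% | 0.25 | 0.025 SD | 5% | 0.507 |
| 20% | 0.5 | 0.10 SD | 18% | 0.528 |
| 20% | 0.8 | 0.16 SD | 29% | 0.543 |

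**False significance favouring the app**

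These rates come from simulation with 14 per arm before exclusions, the asymptotic Mann–Whitney test and 20,000 runs per setting. The nominal rate in this direction is 2.5%.

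| q | s | No exclusion | Rule as written | Same exclusion in both arms |
|---|---|---|---|---|
| 10% | 0.25 | 2.0% | 2.5% | 2.3% |
| 20% | 0.5 | 2.1% | 3.9% | 2.5% |
| 20% | 0.8 | 2.2% | 5.2% | 2.2% |

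**Scale against noise**

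With 14 in Arm A and 14 × 0.8 = 11.2 left in Arm B, the standard error of the difference is √(1/14 + 1/11.2) = 0.40 SD. A bias of 0.10 to 0.16 SD is 25 to 40% of one standard error. It shifts the estimate without dominating it.

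**What the calculation leaves out**

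The 80% app-use rule is a second, separate selection in Arm A. It can also favour the app if patients who keep using it are those whose activity holds up better. It is not counted above, because the proposed change keeps that rule.

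**The case against.** The case for leaving the text alone has several parts.

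- **Per-protocol logic.** The set is meant to reflect adherence to the assigned treatment. A control who uses another reminder app has crossed over, and an Arm A patient who does so has not. This stands, and the point is therefore limited to structured activity.
- **Limited role.** Section 2.5.2 calls the per-protocol results supportive and says that p-values beyond the primary endpoint analysis are read descriptively. Section 2.5.3 says even the primary results are interpreted only descriptively. This stands and keeps the severity low. A reader might infer that the set is there to confirm the primary result, but the text claims only to assess consistency and robustness.
- **Primary result untouched.** The full analysis set uses data whatever the adherence, so the tilt cannot reach the primary comparison. This stands.
- **Assumed size.** The endpoint is a change, so a programme already under way in week 1 raises both weeks and largely cancels. The illustration needs support that starts or intensifies after week 1. This stands and is stated as a condition.
- **Contamination is acknowledged.** The Discussion does list it, but only for the control arm, so this does not answer the asymmetry.

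Two stronger readings are tempting. The first is that the Arm B criterion has no data source, because the nearest row in Table 1 is "Handling smartphones" at baseline. The document does not support this. Table 1 is a condensed article table that also has no row for adverse events or app logs, although sections 2.4.5 and 2.4.3 provide for both. The full protocol or case report form may record outside activity. The second is to add the 80% filter to the bias and quote a much larger share of the planned effect. That needs a correlation between app use and change that appears nowhere in the article, and the result would include a part that the fix does not remove.

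**Conclusion.** The point holds for structured activity. The per-protocol rule treats the same behaviour differently by arm, and the contrast leans towards the app if such programmes raise the week 5 minus week 1 change. Under the assumptions of 20% uptake after week 1 in each arm, a gain of 0.5 to 0.8 SD and no app effect, the false difference is 0.10 to 0.16 SD and false significance favouring the app is about 4 to 5% instead of 2.5%. At 10% uptake and 0.25 SD it is 0.025 SD and of no practical importance. The true uptake and gain are unknown. A reader might infer that the trial's main conclusion is biased, but the document does not support that, because only the supportive analysis is affected. Severity is minor.

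**What to change.** In section 2.5.2, apply the condition of no structured activity intervention outside the trial to both arms. Keep the comparable-app exclusion for Arm B as a crossover criterion, and keep the 80% app-use criterion for Arm A.

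Report per-protocol exclusions by arm and reason; the section already commits to this for the full analysis set. Add a sentence stating that the per-protocol contrast is not a randomised comparison, that selection on app use may still favour Arm A, and that the contrast cannot by itself establish robustness of the full-analysis-set result.

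The cost is a few sentences, best settled before outcome data by arm are seen. There are two drawbacks. A few more Arm A patients may be lost from an already small set. And if the app itself prompts patients to join programmes, excluding them removes part of its effect. The symmetric rule is neutral only when uptake for other reasons is similar in the two arms, and exclusion counts by arm would let readers judge that.
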